**Figure 2 figure2:**
[figure not shown]
Schedule of enrollment, intervention, allocation, and assessments. CaSUN-Info: Cancer Survivors’ Unmet Needs Measure—Information domain; CAT: Chronic Obstructive Pulmonary Disease Assessment Test; EORTC QLQ C30: European Organisation for Research and Treatment of Cancer Quality of Life Questionnaire—Core 30; EORTC QLQ LC13: European Organisation for Research and Treatment of Cancer Quality of Life Questionnaire—Lung Cancer 13; HADS: Hospital Anxiety and Depression Scale; IPAQ-7: International Physical Activity Questionnaire-Short Form; Mini-MAC: Mini-Mental Adjustment to Cancer; mMRC: Modified Medical Research Council; T0 is baseline (before surgery); T1 is 1 month after surgery; T2 is 6 months after surgery; T3 is 1 year after surgery. *Primary outcome.

### Data Monitoring

Although the intervention primarily comprised educational videos and consultations with a family medicine physician, the associated risk to the participants was anticipated to be minimal. Accordingly, the establishment of a formal data-monitoring committee was considered unnecessary. However, procedures for monitoring adverse events and their unintended effects remain in place. The research team regularly reviewed participants’ feedback and outcomes to identify potential concerns. Should any adverse events or unintended consequences arise, they will be addressed promptly, with details reported to the overseeing institutional review board (IRB) at the SMC, as per the standard protocol.

### Statistical Analysis

To assess the effectiveness of LC^3^P, we compared the outcomes between the intervention and control groups at multiple time points. The primary analyses involved independent sample 2-tailed *t* tests for continuous variables and chi-square tests for categorical variables to compare baseline characteristics and outcomes between the 2 groups at each follow-up. To account for repeated measures within participants over time and potential within-subject correlations, a mixed-model repeated-measures analysis was used.

In addition to primary analyses, sensitivity analyses probed the robustness of the trial findings under different assumptions regarding missing data and the effects of protocol adherence on treatment outcomes. This included intention-to-treat and per-protocol analyses. Moreover, subgroup analyses were conducted to examine the variability in treatment effects across different patient characteristics such as age, cancer stage, and the presence of comorbid conditions. All tests were 2-tailed, with a significance level of *P*<.05. To address multiple testing concerns, particularly with numerous secondary outcomes, we used Bonferroni correction or other suitable adjustments to preserve the overall type I error rate. All statistical analyses were conducted using STATA/MP (version 16.0; StataCorp).

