## Methods

### Study Setting

We designed a controlled before-and-after trial at the Samsung Comprehensive Cancer Center of the Samsung Medical Center (SMC), a university-affiliated hospital in Seoul, Republic of Korea, to evaluate the impact of LC^3^P compared to routine care. This design was selected to minimize the risk of information contamination between the control and intervention groups. This risk is particularly pertinent to educational interventions, in which the exchange of information between participants can confound outcomes.

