#### Secondary Outcome Measures

The secondary outcomes were unmet informational needs, quality of life, distress, and symptoms. Unmet informational needs were assessed using the information needs scale (3 items) from the Korean version of the Cancer Survivors’ Unmet Needs scale [26,27]. Health-related quality of life is measured using the Korean version of the European Organisation for Research and Treatment of Cancer Quality of Life Questionnaire—Core 30 [28]. Distress was assessed using the National Comprehensive Cancer Network Guidelines for Distress Management (version 2.2021) [29]. The European Organisation for Research and Treatment of Cancer Quality of Life Questionnaire—Lung Cancer 13 [30], the Chronic Obstructive Pulmonary Disease Assessment Test [31,32], and the modified Medical Research Council dyspnea scale [33] are used to assess the presence and severity of symptoms related to lung cancer.

The Korean version of the International Physical Activity Questionnaire-Short Form is used to identify participants’ levels of physical activity [34]. Depending on the level of activity derived from the questionnaire, patients were categorized into high, moderate, or low groups. The Hospital Anxiety and Depression Scale is a measure of depressive mood [35]. The components of each intervention and the hypothesized effects on the primary and secondary outcomes are shown in Figure S3 in Multimedia Appendix 1.

Sociodemographic variables such as age, sex, and level of education were acquired directly from the participants via self-reported questionnaires. Clinical characteristics, such as cancer stage, type of treatment, and postsurgical complications, were obtained from electronic medical records.

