### Recruitment

Patients scheduled for pulmonary resection were recruited as controls to prevent contamination. The recruitment and study period for the control group were completed before the start of the intervention to ensure no overlap. Subsequently, recruitment to the intervention group began.

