## Results

The historical control group (n=441) was recruited from September 8, 2021, to April 20, 2022, and the intervention group (n=350) was recruited from April 22, 2022, to October 17, 2022. All statistical analyses will be performed upon completion of the study.

As part of a nationally funded study, the results and details of the procedures will be made publicly available upon completion. The findings of this study will be actively shared through publications in peer-reviewed academic journals and at national and international scientific conferences. Regarding the intervention, the content and access to the educational videos will be refined based on the feedback patients provide on their first follow-up visit and will be made available on YouTube and to other health care professionals within the same health care institution, including oncologists and oncology nurses. The full protocol for this study is currently available at the ClinicalTrials.gov (NCT05078918). The raw data for this study will be shared upon request.

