### Limitations

Despite these advantages, this study has some limitations that must be addressed. First, the design of the intervention might be more appealing to participants who are actively seeking ways to adapt to life after cancer, as opposed to those who are less motivated or indifferent about making such adjustments. In addition, although the use of a historical comparison group was intended to minimize the impact of exposure to our intervention in patients with lung cancer, the limitations of using a nonparallel comparison group should not be ignored. Second, socioeconomic and geographic disparities among older patients with cancer could affect accessibility to web-based educational videos. Although disseminating educational videos through web-based platforms allows cancer survivors to access as much information as they need at their convenience, it can be difficult for survivors with limited access to technology to access this information. If found to be promising, future studies should address the disparities in accessing web-based educational videos. Finally, the trial was registered after the recruitment commenced. However, there were no changes in the study design, measurement, or analysis methods after receiving the initial ethics approval.

In conclusion, the LC^3^P represents a proactive, holistic prehabilitation intervention aimed at supporting lung cancer survivors, as they navigate the transition to life after treatment. Our findings highlight the impact of early informational support on patients’ psychological adaptation and postdiagnosis stress management. This could potentially establish a new standard for the timing and delivery of survivorship care, emphasizing the benefits of early intervention.

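### The tests named as primary compare two non-randomised, sequential cohorts at follow-up without using the baseline score, and the mixed model is not specified in a way that repairs this

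*Protocol article*

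**What the plan says.** Study Setting gives the design: "We designed a controlled before-and-after trial". Results gives the cohorts. For the controls it reports: "The historical control group (n=441) was recruited from September 8, 2021, to April 20, 2022". For the patients offered the programme, who came second, it reports: "the intervention group (n=350) was recruited from April 22, 2022, to October 17, 2022". Group membership is therefore decided by calendar period.

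The primary outcome is the Mini-MAC at T2, and Data Collection has outcomes assessed at T0 as well as at three follow-ups. Prognostic data are also held: "Sociodemographic variables such as age, sex, and level of education were acquired directly from the participants via self-reported questionnaires", with cancer stage taken from the medical record.

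Statistical Analysis names, as the primary analyses, independent-sample two-tailed t "tests for continuous variables and chi-square tests for categorical variables to compare baseline characteristics and outcomes between the 2 groups at each follow-up". The next sentence adds a mixed-model repeated-measures analysis, and the only reason given for it is repeated measurement and correlation within participants. The sensitivity analyses listed concern missing data and adherence. Age, stage and comorbidity appear only as subgroup factors. The Limitations section concedes that "the limitations of using a nonparallel comparison group should not be ignored", but no stated analysis answers that concession.

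**The concern.** In a randomised trial, a crude t test at follow-up is unbiased and merely inefficient. Here nothing balances the cohorts. If the later cohort starts with a different Mini-MAC level, or a different mix of age, education or stage, the part of that difference which persists to T2 enters the estimated effect of the programme. The protocol itself suggests one possible route: the Limitations section says the programme may attract people already looking for ways to adapt, and only the second cohort was recruited to receive it. That trait lies close to what the Mini-MAC measures.

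Testing baseline characteristics for significance describes imbalance but does not remove it, and a non-significant result does not show that the cohorts are comparable. At stake are the validity of the primary estimate and its precision.

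**Working it through.** **Inputs from the documents.** Enrolled 441 and 350 (Results); dropout 16%, effect size 0.25 and 252 per group (Sample Size Calculation); two-sided 5% level (Statistical Analysis).

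**Inputs assumed.** The T0 gap d between cohorts (in SD) and the T0-T2 correlation r are not given, so ranges are shown. Power is not stated; 80% is inferred in step 1.

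**1. The plan's own figure.** n per group = 2 × (1.960 + 0.842)² / 0.25² = 251.2, rounded up to 252 (the exact t-test solution is 252.1). Power of 90% would give 337, and a one-sided test at 80% power would give 198. So 252 reproduces as a plain two-sample t test at 80% power, and 252 / 0.84 = 300. The sizing, like the named test, assumes an unadjusted comparison.

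**2. Standard error of the crude T2 difference.** 441 × 0.84 = 370.4 and 350 × 0.84 = 294. SE = √(1/370.4 + 1/294) = 0.078 SD.

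**3. False-positive rate with no treatment effect.** If the cohorts differ at T2 only through T0, the expected T2 difference is r × d, and the rejection rate is P(|N(rd/SE, 1)| > 1.96). Example: d = 0.20 and r = 0.5 give a bias of 0.10 SD; 0.10 / 0.078 = 1.28; the rejection rate is 24.9%.

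| T0 gap d | r = 0.3 | r = 0.5 | r = 0.7 | gap persists in full |
|---|---|---|---|---|
| 0.10 SD | 6.7% | 9.8% | 14.6% | 24.9% |
| 0.20 SD | 12.0% | 24.9% | 43.3% | 72.6% |
| 0.25 SD | 16.0% | 36.0% | 61.0% | 89.2% |

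Simulated t tests agree closely (for example 25.9% at d = 0.20, r = 0.5).

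**4. What the baseline test would show.** With 441 and 350 at T0, SE = √(1/441 + 1/350) = 0.0716 SD. A true gap of 0.10 SD would be significant only 28.7% of the time, so it would be missed about 71% of the time.

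**5. What adjustment does (simulated, d from 0.10 to 0.25, r from 0.3 to 0.7).**
- Cohort acts on T2 only through T0: ANCOVA on T0 rejects 4.3% to 5.3%; a change-from-T0 contrast rejects about 8% to 47%.
- Cohort shift persists in full: ANCOVA rejects about 8% to 63%; the change-from-T0 contrast rejects 4.4% to 5.8%.

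The two are therefore not interchangeable. ANCOVA under-corrects a persistent shift, and the change contrast over-corrects one that fades.

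**6. Precision.** ANCOVA multiplies the SE by √(1 − r²). From 0.078 SD it falls to 0.0745, 0.0677 and 0.0558 SD at r = 0.3, 0.5 and 0.7. The 252 per group becomes 252 × (1 − r²): 230, 189 and 129.

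**The case against.** The strongest reply concerns the mixed model. It stands in the same paragraph as the t tests, and only the next paragraph turns to analyses beyond the primary ones, so it may itself be among the primary analyses. With outcomes at T0 to T3 it could carry T0 as a response or a covariate and give a baseline-referenced contrast. This stands in part: a reader might infer that nothing in the plan could use T0, and the text does not support that. But the only purpose given is within-subject correlation, no baseline term or contrast is stated, and the crude test is expressly called primary. The model as described does not cure it.

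Second, a condensed article may leave covariate lists and model terms to a fuller document. That is fair, and the absence of a list or of a propensity analysis is not the fault raised here. The fault is what the article does state: a crude test labelled primary in a design where it is not valid without adjustment.

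Third, no baseline gap is shown. Both cohorts come from one centre under one set of criteria, and the recruitment periods are two days apart. This also stands; the figures above say what would follow from a gap, not that one exists.

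Fourth, the before-and-after label need not refer to T0. It may mean the control cohort recruited before the programme began. The point does not depend on that label.

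**Conclusion.** The concern holds in a limited form. The tests named as primary are unadjusted comparisons of non-randomised, sequential cohorts. They ignore a baseline score and prognostic variables that the trial collects, and the accompanying mixed model is not specified so as to repair this.

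The error rates in the table are hypothetical. They rest on the assumed gap and correlation, on 16% dropout in each cohort and on a normal approximation. At the mild end (gap 0.10 SD, r = 0.3) the inflation is slight, to 6.7%. With a gap of 0.20 SD and r = 0.5 it reaches about one in four. A gap of 0.25 SD that persisted in full would equal the whole design effect.

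Two stronger readings are tempting and not supported. One is that any baseline difference passes whole into the treatment effect: only the carried-over part does, r × d if the gap acts through T0, and all of it only if the shift persists. The other is that adjustment would make the comparison unconfounded: it deals with measured differences and leaves unmeasured calendar-time effects, a limit of the design that the article acknowledges.

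**What to change.** - Name one adjusted T2 group contrast as the primary analysis: ANCOVA, or the planned mixed model with a T0 term. Adjust for T0 Mini-MAC and prespecified pre-surgical covariates: age, sex, education, cancer stage and comorbidity.
- Do not adjust for post-surgical complications. They arise after the point at which patients are urged to have seen the first video, so they may be affected by the intervention.
- Report a change-from-T0 (group-by-time) contrast as a sensitivity analysis, because ANCOVA under-corrects a persistent cohort shift. State what each assumes.
- Keep the crude t and chi-square tests as descriptive, and show baseline imbalance by standardised differences instead of P values.
- Confirm that T0 was completed before any video was seen. Data Collection places T0 immediately after enrolment, and Delivery of the Intervention sends the first link at enrolment.
- State that unmeasured calendar-time confounding remains. A propensity-weighted analysis is optional.

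The cost is a few sentences of analysis wording and a few lines of Stata. No extra patients are needed. T0, age, sex, education and stage are collected, and comorbidity is already planned for subgroups. Results says the analyses await study completion, and Ethical Considerations provides for amending them, so the change should be recorded before the outcome data are analysed.

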### Data Collection

The clinical trial procedure and intervention are outlined in Figure 1, with the outcomes assessed at baseline (T0), 1 month (T1), 6 months (T2), and 1 year (T3) postoperatively. Baseline data will be collected before surgery and immediately after enrollment. To enhance participant retention and adherence, individuals in both groups received a small token of appreciation upon completion of each of the 3 postoperative follow-up assessments (T1-T3). For participants who discontinued or deviated from the intervention protocols, the data collected up to the point of departure were included in the intention-to-treat analysis to maintain the robustness of the trial results and minimize the impact of attrition bias. The data obtained from self-administered questionnaires were coded and stored in password-encrypted Microsoft Excel (Microsoft Corp) files on a secure computer server. The specific variables measured at each time point are listed in Figure 2.

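### Physical activity, an ordered three-level outcome, is compared by a chi-square test that uses neither the order nor the baseline category

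*Protocol article*

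**What the plan says.** Under Secondary Outcome Measures, the protocol article scores the physical activity questionnaire into levels: "patients were categorized into high, moderate, or low groups". These levels have a natural order.

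Under Statistical Analysis, the analyses called primary are t tests for continuous variables and "chi-square tests for categorical variables"; they serve to compare the groups both on baseline characteristics and on outcomes at every follow-up. As written, activity level falls under the chi-square test at T1, T2 and T3. The next sentence adds that, to handle repeated measures within participants, "a mixed-model repeated-measures analysis was used". It does not say which outcomes the model covers, whether baseline enters it, or whether any form for ordered categories is meant.

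Under Data Collection, the article has "outcomes assessed at baseline (T0), 1 month (T1), 6 months (T2), and 1 year (T3) postoperatively", so a T0 value is part of the design. Under Results, the control group is described as historical: 441 controls were recruited first and 350 intervention participants afterwards.

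**The concern.** A Pearson chi-square test on a two-by-three table has 2 degrees of freedom and asks only whether the two distributions differ in any way. If the programme moves people up or down the activity scale, an ordinal test puts its power into that single direction, whereas chi-square spreads it over patterns that would not be read as benefit or harm. A significant chi-square also comes without an effect estimate: it does not by itself say whether activity rose or by how much.

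Separately, the test has no place for the T0 category. In a randomised trial that would mainly waste precision. Here the cohorts are sequential, so any difference in activity already present before surgery can pass into the follow-up comparison.

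**Working it through.** **The plan's own figure.** The only stated sample size concerns the primary outcome: 252 per group at an effect size of 0.25, raised to about 300 for 16% dropout. No power is stated. Assuming 80% power and two-sided 0.05, n = 2(1.96 + 0.8416)² / 0.25² = 251.2, that is 252, and 252 / 0.84 = 300. Both figures reproduce. Nothing below depends on them except the 16% dropout rate. The plan gives no power figure for any categorical outcome.

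**Inputs.**
- Evaluable numbers: 441 × 0.84 = 370 controls and 350 × 0.84 = 294 intervention participants (recruited numbers from Results, dropout from Sample Size Calculation).
- Two-sided significance level 0.05 (Statistical Analysis).
- Assumed, because the article gives neither: the control split over the three levels, and a common odds ratio (OR) under proportional odds.

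**Worked case: control split 40/40/20, OR 1.5.**
1. Control cumulative odds are 0.4/0.6 = 0.667 and 0.8/0.2 = 4. Dividing by 1.5 gives 0.444 and 2.667, so the intervention cumulative proportions are 0.308 and 0.727 and the split is 30.8/42.0/27.3.
2. Pooled proportions p̄ = (370 × control + 294 × intervention) / 664 are 0.359, 0.409 and 0.232.
3. Chi-square noncentrality = (370 × 294 / 664) × Σ(difference² / p̄) = 7.77. With 2 degrees of freedom, power is 0.704.
4. Ordinal test: V = n₁n₂N / [3(N + 1)²] × (1 − Σp̄³) = 54.44 × (1 − 0.127) = 47.5. Power = Φ(ln 1.5 × √47.5 − 1.96) = Φ(2.795 − 1.96) = 0.798.
5. Loss: 0.798 − 0.704 = 0.094, about 9 points.

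**Range over odds ratios and splits** (same formulas, 370/294; each cell is chi-square / ordinal power):

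| Control split | OR 1.4 | OR 1.5 | OR 1.6 |
|---|---|---|---|
| 30/45/25 | 0.531 / 0.638 | 0.700 / 0.796 | 0.828 / 0.898 |
| 40/40/20 | 0.534 / 0.640 | 0.704 / 0.798 | 0.832 / 0.900 |
| equal thirds | 0.540 / 0.647 | 0.710 / 0.804 | 0.836 / 0.904 |

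A simulation of 20,000 draws at 40/40/20, comparing chi-square with a tie-corrected Wilcoxon test, gave 0.537 / 0.644, 0.702 / 0.798 and 0.839 / 0.903. More skewed splits at OR 1.5 gave similar losses: 0.69 / 0.79 for 20/40/40 and 0.67 / 0.76 for 60/30/10. Both tests rejected about 5% of the time under the null. The loss is therefore about 6 to 11 points.

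**Effect of the T0 category.** A smaller simulation used 400 replicates, a three-level outcome and an assumed latent baseline–outcome correlation of 0.5. Rejection rates were:

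| Scenario | Chi-square | Wilcoxon | Ordinal model with T0 category |
|---|---|---|---|
| True effect 0.20 SD, no cohort difference | 0.51 | 0.60 | 0.72 |
| No effect, cohorts differ by 0.2 SD at T0 and follow-up | 0.52 | 0.64 | 0.30 |

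The first row shows a gain of about 20 points from using order and baseline together. The second shows that order alone does not help with cohort bias: the unadjusted ordinal test rejects more often than chi-square. Adjustment for the T0 category lowers false rejection from about 52% to about 30%, still far above 5%.

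**The case against.** Chi-square on a two-by-three table is a valid test. It needs no proportional-odds assumption, and reported percentages would show direction. The power figures come from data that satisfy proportional odds exactly, which favours the ordinal test. Activity is not among the four outcomes that open the secondary outcomes section; it comes in the following paragraph under the same heading. The article is condensed and points to a fuller protocol, where outcome-level models might be set. A mixed model is also planned.

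Much of this stands, and it is why the point is minor. It does not remove the point: the article does not stay silent but names a test, and that test covers activity level as written. The mixed-model sentence might cover activity, but nothing says so.

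Three stronger readings are tempting and not supported.
- A reader might infer that dyspnea grade is also tested by chi-square. The article lists "the modified Medical Research Council dyspnea scale" only as a symptom measure and never says whether it is analysed as a score or as categories.
- A reader might infer a stated directional hypothesis for activity. The hypothesis in the shown text concerns psychological adjustment; hypothesised effects on secondary outcomes are referred to a supplementary figure that is not shown, and the analysis section says "All tests were 2-tailed, with a significance level of" 0.05.
- A reader might infer that ignoring the order causes cohort bias. It costs power only. The bias comes from the unadjusted historical comparison, and the Limitations section itself acknowledges the non-parallel control group.

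**Conclusion.** The point holds for physical activity. The plan assigns an ordered outcome, measured at baseline in a non-randomised design, to a test that uses neither the order nor the baseline. The cost of ignoring the order is about 6 to 11 power points at 370/294, assuming proportional odds, odds ratios of 1.4 to 1.6 and the splits shown. If a Bonferroni correction were applied over the eight non-primary instruments (an assumption, significance level 0.05/8 = 0.00625), power at OR 1.5 and 40/40/20 would be 0.41 against 0.52, so the gap persists. The benefit of the T0 category rests on further assumptions and a small simulation, and is best read as indicative. Severity is low: an inefficient and uninformative choice for a non-primary outcome, not an invalid one, with no bearing on the primary result.

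**What to change.** For activity level, replace the chi-square test of outcomes with a proportional-odds logistic model containing group, T0 activity category and prespecified patient characteristics already collected, such as age, sex and cancer stage. The covariates must be named, because the article lists none for any model. Report the common odds ratio with its 95% confidence interval at T2, alongside the percentages in each level. State how the dyspnea scale is analysed, and apply the same model to it only if it is treated as categorical. Chi-square can stay for unordered variables, and the three-level scoring needs no change.

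The cost is a sentence or two in the analysis section and a standard command in the software already named; no new data are needed. The article says the analyses await study completion, so on its own account this could be settled beforehand. The proportional-odds assumption must be checked, and the report should say that baseline adjustment reduces but does not remove bias from sequential cohorts.

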### Sample Size Calculation

Based on the primary hypothesis that the intervention group would demonstrate a 25% better psychological adjustment to cancer at 6 months after surgery than the control group, initial calculations with an effect size of 0.25 indicated that 252 participants per group would be required. We aimed for a sample size of approximately 300 per group to account for a dropout rate of 16%. However, to increase the robustness of our findings, allow for potential subgroup analyses, and ensure that the study had sufficient power to detect smaller effect sizes, we enrolled 400 participants per group. The sample size significantly exceeded the required number based on our initial estimates, thereby enhancing the statistical power and potential impact on the study's outcomes.

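### Two sequential, non-randomised cohorts are compared at baseline only by significance tests and at 6 months by an unadjusted t test, so an imbalance too small to flag can still bias the primary result

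*Protocol article*

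**What the plan says.** The Recruitment section of the protocol article describes sequential cohorts with no concurrent control: "The recruitment and study period for the control group were completed before the start of the intervention to ensure no overlap". The Results section gives 441 historical controls and 350 intervention participants.

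The Statistical Analysis section puts independent-samples t tests for continuous variables under the primary analyses, together with "chi-square tests for categorical variables to compare baseline characteristics and outcomes between the 2 groups at each follow-up". The threshold is common to all tests: "All tests were 2-tailed, with a significance level of *P*<.05". A mixed model for repeated measures follows. Its stated purpose is to handle repeated observations and the correlation within a participant, and no covariate is named for it. The section names no other between-cohort baseline measure and no adjusted comparison.

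The Limitations section concedes that "the limitations of using a nonparallel comparison group should not be ignored", but offers no analytic remedy.

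The planning effect is in the Sample Size Calculation section: "initial calculations with an effect size of 0.25 indicated that 252 participants per group would be required".

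**The concern.** Nothing in this design makes the two groups alike at baseline. Patients were enrolled in different months, so they may differ in case mix, treatment or preoperative state of mind. What matters for the 6-month comparison is how large any difference is and how strongly the variable predicts 6-month Mini-MAC. A P value measures neither, because it also depends on the number of patients.

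The t test on the 6-month outcome takes no account of baseline differences. An imbalance therefore passes into the primary estimate in proportion to how strongly the variable predicts the outcome, whether or not the baseline test was significant. Even when a baseline test is significant, the article states no consequence for the outcome analysis. At stake is how much of a 6-month difference can be credited to the programme rather than to a difference that was there before surgery.

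**Working it through.** **The plan's own figure.** For two means with a standardised difference of 0.25, two-sided 5% and 80% power (power is not stated, so 80% is assumed):

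n per group = 2 × (1.960 + 0.842)² / 0.25² = 251.2, rounded up to 252.

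With 16% dropout, 252 / 0.84 = 300. Both stated figures reproduce, which supports reading 0.25 as a difference in SD units.

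**What the baseline test can see.** Inputs: 441 and 350 (Results), two-sided 5% (Statistical Analysis).

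- SE of a standardised difference = √(1/441 + 1/350) = 0.0716.
- Smallest significant difference = 1.96 × 0.0716 = 0.140 SD.
- Probability of significance at true imbalance d = Φ(d/SE − 1.96) + Φ(−d/SE − 1.96).

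| True imbalance (SD) | Significant | Missed |
|---|---|---|
| 0.10 | 28.7% | 71.3% |
| 0.14 | 49.8% | 50.2% |
| 0.20 | 79.8% | 20.2% |
| 0.25 | 93.7% | 6.3% |

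**What a missed imbalance does at 6 months.** Inputs: the 16% planning dropout, applied to both cohorts (assumed), and a correlation r between baseline and 6-month Mini-MAC (not in the document, assumed 0.4 to 0.7).

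- Numbers at 6 months: 441 × 0.84 = 370.4 and 350 × 0.84 = 294.
- SE of the 6-month difference = √(1/370.4 + 1/294) = 0.0781 SD.
- Shift in an unadjusted comparison = r × 0.14.
- Rejection rate with no intervention effect = Φ(shift/0.0781 − 1.96) + Φ(−shift/0.0781 − 1.96).

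| r | Shift (SD) | Share of 0.25 | Rejection with no effect |
|---|---|---|---|
| 0.4 | 0.056 | 22% | 11% |
| 0.5 | 0.070 | 28% | 15% |
| 0.7 | 0.098 | 39% | 24% |

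At r = 0.3 the shift is 0.042 SD, 17% of the planning effect, with 8% rejection.

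**How the 0.14 is read.** The table treats 0.14 SD as a true difference between the populations enrolled. If it is instead the observed difference among the patients analysed, and is held fixed, the remaining standard error is 0.0781 × √(1 − r²). The rejection rate is then Φ((shift − 1.96 × 0.0781)/that SE) plus the opposite tail: 9%, 11% and 16% for r = 0.4, 0.5 and 0.7. The shift and its share of 0.25 are the same on either reading.

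**The case against.** **The article sets no comparability rule.** A reader might infer that a non-significant baseline test will be reported as showing comparable groups, or that covariates will be chosen by baseline P values. The text says neither. It says only that baseline characteristics are compared, and the Limitations section is candid about the historical control. This objection stands. The point is confined to the methods the article does state.

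**Baseline tests also raise false alarms.** A reader might add that such tests flag trivial differences by chance. That does not hold here. At 441 and 350, a significant continuous variable has an observed difference of at least 0.14 SD, which is not trivial if the variable predicts Mini-MAC. The familiar argument from randomised trials, that the null is true by design, does not apply to sequential cohorts.

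**A standardised-difference threshold would do better.** As a rule for choosing covariates, it would not. With SE 0.0716 and truly equal cohorts, an absolute value above 0.10 arises by chance for 16% of variables. Over 15 independent variables (an illustrative number), the chance of at least one is 1 − 0.838¹⁵ = 93%. Selection would still be driven by the observed data.

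**The bias comes from lack of adjustment, not from the baseline table.** This is correct and shapes the fix: changing a table column alone alters no result.

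**The mixed model may deal with it.** Outcomes are assessed from baseline, and depending on its specification the model could account for the baseline score. The full analysis plan is not shown and may name covariates. But the article gives the model a different purpose, and it places the unadjusted t test among the primary analyses.

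**Large imbalances are caught.** A true 0.25 SD difference is significant 94% of the time. The weakness lies at about 0.10 to 0.20 SD, and detection has no stated consequence anyway.

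**Conclusion.** The point holds as a minor but worthwhile correction to a stated analysis choice. For two non-randomised cohorts, the article's only between-group baseline method is a significance test, and its stated 6-month t test is unadjusted. Imbalances below 0.14 SD are non-significant. One of that size in baseline Mini-MAC would carry 0.056 to 0.098 SD into the primary comparison, 22% to 39% of the planning effect, with about 11% to 24% rejection under no effect.

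These sizes rest on an assumed correlation of 0.4 to 0.7, on 16% dropout in both cohorts, and on 0.14 SD being a true difference; the rejection rates are 9% to 16% if it is an observed one. The direction of any imbalance is unknown, so the shift could favour or mask the programme. The documents do not show that an imbalance exists.

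**What to change.** In the Statistical Analysis section, define the primary 6-month Mini-MAC comparison as one adjusted for preoperative Mini-MAC and a short list of prognostic covariates named in advance from those already collected (for example age, sex, education and cancer stage). State that these covariates enter whatever their baseline P values. This can be an analysis of covariance at 6 months, or the mixed model with those terms written in.

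In the baseline table, report standardised differences as description, and say that they are not used to select covariates.

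The cost is a few sentences and one table column. Sociodemographic and clinical variables and baseline outcomes are already collected, and the Results section says that the analyses are still to be performed. Adjustment deals with measured imbalance only. Unmeasured differences and calendar-time changes between the two recruitment periods are untouched, so the caveat in the Limitations section should stay.
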